### Allocation of patients

Patients will be randomised to one of two study arms. The random allocation sequence will be generated by computer and incorporated into a Microsoft Access programme written for patient recruitment, randomisation and event recording. Stratified block randomisation will be performed according to patient status on admission (Glasgow coma score 14–15/15, Glasgow coma score <14/15).

The allocation sequence will be generated independently by the study statistician and programmer, who will have no role in patient recruitment, treatment or assessment. Variable block sizes of 3, 6 and 9 will be used to allocate patients in equal numbers to each treatment group i.e. ratio 1:1.

Participants will be recruited and randomised by a study doctor at the bedside using a dedicated handheld computer at each study hospital. Randomisation will occur after the patient's baseline data have been entered and receipt of consent noted, and cannot be manipulated by study doctors. The recruiting doctor will be unable to predict allocation before randomisation.

All practical steps have been taken to avoid bias: (i) the randomisation program has been designed to be rapid and simple to operate, and yet remain independent of the investigators; (ii) the next treatment allocation cannot be predicted in advance; (iii) the primary outcome, vital status at discharge, is unambiguous, and the secondary outcomes are objective; (iv) all outcomes are recorded by the study team, not other hospital physicians;

(v) patient follow-up should be near 100% complete; and (vi) the analysis will be performed on an intention-to-treat basis.

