**Methods/Design:**

We have designed an RCT assessing the effectiveness of multiple gastric lavages in adult OP self-poisoning patients admitted to three Chinese hospitals within 12 hrs of ingestion. Patients will be randomised to standard treatment plus either a single gastric lavage on admission or three gastric lavages at four hour intervals. The primary outcome is in-hospital mortality. Analysis will be on an intention-to-treat basis. On the basis of the historical incidence of OP at the study sites, we expect to enroll 908 patients over three years. This projected sample size provides sufficient power to evaluate the death rate; and a variety of other exposure and outcome variables, including particular OPs and ingestion time. Changes of OP level will be analyzed in order to provide some toxic kinetic data.

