Patients will be first managed on the medical ward. Seriously ill patients, as judged by the medical team, will be transferred to ICU as a bed becomes available.

Criteria for intubation include respiratory rate of less than 10 breaths/minute, abdominal breathing, failure of non-invasive methods to maintain a patent airway, or the fraction of oxygen pressure to its concentration is lower than 300. Hypotensive patients, unresponsive to atropine and fluid resuscitation, are treated with dopamine plus dobutamine as necessary.

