### Trial interventions and study procedures

Patients will be placed in left lateral position and a nose-gastric tube placed through a nostril. Once in the stomach, its position will be confirmed by aspirating gastric content and auscultating over the stomach. The gastric content will be sucked out first and then 300 ml of water at room temperature pushed in. The water will then be aspirated completely and another 300 ml administered. The above procedures will be repeated until the aspirated water is without smell and clear – this end point will be judged by at least two doctors.

The above procedure will be repeated 4 hours and 8 hours after the first gastric lavage in the group of patients receiving multiple lavages. 24 hours after admission, and after gastric lavage and sample collection has been finished in all groups, the gastric tube will be pulled out.

The procedure will be done by skilled medical staff. Vital body signs, including ECG (electric cardiac graph) monitor, blood pressure, heart rate, respiratory rate, and pulse oxygen saturation will be monitored throughout the lavage. Patients will also be monitored for complications such as aspiration. There should be no major problem with compliance since the lavage will be given by the study team.

A 10 ml blood sample will be taken using a sterile syringe and needle from each patient on recruitment. Further 5 ml blood samples will taken at one, four and twelve hours post-treatment, and then at daily intervals until discharge or death, from a subset of patients. Whether a needle or indwelling cannula is used will be determined by the wishes of the patient. The identity and blood concentration of the poison will be assayed retrospectively in a subset of patients due to limited laboratory facilities.

A 10 ml sample of gastric aspirate will be taken at the beginning of each gastric lavage so that the concentration of pesticide present in the stomach can be calculated. The volume of fluid aspirated before the first 300 ml of water is given will be recorded.

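### Hospital is neither a stated stratum nor a factor in the stated primary test, although each of the three hospitals allocates from its own handheld; the gain from adding it is modest but cheap

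*Protocol article*

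**What the plan says.** Under Allocation of patients, the protocol article gives the stratification rule as "Stratified block randomisation will be performed according to patient status on admission (Glasgow coma score 14–15/15, Glasgow coma score <14/15". No other factor is listed. The same section says "Participants will be recruited and randomised by a study doctor at the bedside using a dedicated handheld computer at each study hospital", with a computer-generated sequence built into an Access programme. It does not say whether each device carries its own sequence or all three draw on one.

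Statistical analysis gives the primary mortality comparison as a chi-squared test, or Fisher's exact test if appropriate, by intention to treat. It names no stratum or covariate for that test.

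Three other places bear on whether hospital could matter:

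- The end of each lavage is a judgement made by two or more doctors: "The above procedures will be repeated until the aspirated water is without smell and clear – this end point will be judged by at least two" (Trial interventions and study procedures).
- On intensive care, "Seriously ill patients, as judged by the medical team, will be transferred to ICU as a bed becomes available" (Patient management). Ward teams decide on intubation and ICU transfer independently of study doctors.
- Sample size puts in-hospital mortality at 15% or more in all three hospitals and gives no separate rates.

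**The concern.** In a three-hospital trial of a procedure delivered by local teams, hospital is a natural prognostic factor. It may carry differences in case mix, ICU access and intubation practice. The article leaves it out of both the stated allocation rule and the stated primary test, and each reading of the handheld arrangement leaves something to settle.

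- **One shared sequence.** Blocking within coma score balances the arms over the whole trial but not within a hospital. The article also does not say how separate devices would draw from one list in order.
- **One sequence per handheld.** Allocation is then blocked by hospital in practice. The stated stratification rule is incomplete, and the unadjusted test ignores a factor that the randomisation used.

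What is at stake is some precision, and agreement between the analysis and the randomisation. The validity of the comparison is not at stake.

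**Working it through.** **The plan's own figure.** Sample size gives 454 per arm for 15% against 9%, alpha 5%, power 80%. Sidedness is not stated; two-sided fits. With unpooled variance, n = (1.96 + 0.8416)² × (0.15 × 0.85 + 0.09 × 0.91) / 0.06² = 7.849 × 0.2094 / 0.0036 = 456.6, so 457. The pooled-variance formula gives 460. Power at 454 is 79.5%. The figure reproduces closely, and nothing below changes it.

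**Share of variance between sites.** Site sizes and rates are not in the article. I assume equal thirds and rates that respect the 15% floor. With mean risk p and between-site variance V, the share of the variance of the mortality difference that lies between sites is V / [p(1 − p)]. The part of the difference due to chance site imbalance has SD √(2V/454).

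| Assumed site rates | p | V | SD from site imbalance | Share of variance | SE of difference, unadjusted | SE, site component removed |
|---|---|---|---|---|---|---|
| 15/20/25% | 0.20 | (0.05² + 0 + 0.05²)/3 = 0.00167 | 0.27 points | 0.00167/0.16 = 1.0% | √(2 × 0.16/454) = 2.65 points | 2.64 points |
| 15/25/35% | 0.25 | (0.10² + 0 + 0.10²)/3 = 0.00667 | 0.54 points | 0.00667/0.1875 = 3.6% | √(2 × 0.1875/454) = 2.87 points | 2.82 points |

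The last column is the unadjusted SE × √(1 − share). This variance is not extra. With a shared list it already sits inside the p(1 − p) that the chi-squared test uses. Stratifying takes it out.

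**If each handheld has its own sequence.** The unadjusted test then uses an SE that is slightly too large. Treating sites as perfectly balanced, the real two-sided error at a cut-off of 1.96 is that of a normal deviate beyond 1.96/√(1 − share). This is 4.9% for 15/20/25% and 4.6% for 15/25/35%, so the test is mildly conservative.

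**Arm sizes within a hospital.** A simulation of 908 patients (1,500 runs per scenario) assumed equal sites of about 303 and a 50:50 coma-score split. Because "Variable block sizes of 3, 6 and 9 will be used to allocate patients in equal numbers to each treatment group i.e. ratio 1:1" includes odd sizes that two equal arms cannot fill, the spare place was assigned at random.

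- Shared list: the within-site difference in arm sizes has SD 14–15 and 95th percentile 28–29. As a check, √(303 × 2/3) = 14.2.
- List per hospital: SD about 6, 95th percentile 11–12.

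**Effect on the mortality difference.** The simulation used rates of 10/15/20% and 5/15/25%, which fall below the article's floor. The shift caused by site imbalance depends only on the gaps between sites, which are the same as in the table, so it carries over.

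- Shared list: SD 0.28 and 0.53 points, 95th percentile 0.5 and 1.0 points.
- List per hospital: 95th percentile 0.2 and 0.35 points.

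Null rejection was about 4–6% under both schemes (simulation error about 0.6 points). Power, run for 10/15/20% only, was 79–81% under both.

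**The case against.** The strongest reply is that "using a dedicated handheld computer at each study hospital" may already mean one sequence per hospital. Within-site balance would then exist in practice, and how lists are loaded is a detail that an article can leave to the full protocol. This stands in part: the text does not settle the point, so it cannot be said that the arms will be unbalanced within a site. It does not dispose of the matter, because the stated primary test would then omit a factor used in allocation. A fuller analysis plan may add a hospital term, but the article does state the primary test, and states it without one.

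A reader might infer that the hospitals are known to differ in operators or ICU access. The article does not say so. It describes skilled staff, at least two doctors judging the lavage end point, agreed management protocols and a treatment protocol used across centres. Differences between sites are plausible, not documented.

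A reader might also infer bias or a raised false-positive rate. Neither follows: any imbalance arises by chance under randomisation, and error rates stay near 5% or slightly below.

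Nor does a shared list spoil comparisons within a hospital. They remain randomised. In a site of 150, simple chance gives a 95% range of 75 ± 1.96 × √150/2, or 63 to 87. Even that extreme split raises the variance by only 2.6% over 75 against 75 (1/63 + 1/87 = 0.0274 against 2/75 = 0.0267). The article plans no between-hospital comparison.

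Finally, stratifying by coma score alone is a valid choice in a trial of this size. That is so, and it is why this is an improvement to make, not an error to correct.

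**Conclusion.** The point holds in a limited form. Hospital appears in neither the stated stratification nor the stated primary test, and the article leaves open whether the handhelds carry separate sequences. Either way the comparison is unbiased and its type I error is not inflated. The precision at issue is about 1% to 3.6% of the variance of the mortality difference, which lowers its SE from 2.65 to 2.64 points or from 2.87 to 2.82 points, against a target difference of 6 points. These sizes rest on assumed equal sites and assumed rates of 15/20/25% and 15/25/35%. If the hospitals have nearly the same mortality the gain is close to nil; a wider spread would raise it. The case for acting is that the change is nearly costless and brings the analysis into line with the randomisation under either reading.

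**What to change.** Generate a separate permuted-block sequence for each hospital within each coma-score stratum (3 × 2 = 6 strata), load it on that hospital's handheld, and say so under Allocation of patients. If the handhelds already work this way, a sentence saying so is enough. In Statistical analysis, stratify the primary mortality comparison by hospital and coma score, for example with a Mantel-Haenszel risk difference and relative risk.

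The cost is a change to the allocation lists, best made before the first patient, and a stratified analysis in place of a single two-by-two table. The analysis change can be made at any time before the outcome data are seen. Sample size is unaffected.

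There are two small downsides. Six strata can leave up to six incomplete blocks among 908 patients. In an open trial, doctors who see every local allocation can guess block ends slightly more easily than with a shared list; variable block sizes limit this. The odd block sizes are a separate matter, but they need settling when the sequences are generated.

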### Outcomes

The primary outcome is all-cause mortality during hospital admission.

Secondary outcomes include proportion of patients requiring intubation for respiratory failure; period of ventilation; proportion of patients developing the intermediate syndrome; and 50% recovery time for red cell acetylcholinesterase enzyme activity.

### Sample size

In all three patient enrolled hospitals, at least 15% of poisoned patients die before discharge[6]. An absolute reduction of 6% will be clinically important. In order to be able to detect whether multiple gastric lavage reduces the death rate from 15% to 9%, with a significance level (alpha) of 5% and a power of 80%, a minimum of 454 patients must be recruited to each arm of the trial (i.e. 908 patients in total).

There should be no loss to follow up for the primary outcome. Patients will either be discharged alive from the wards or their bodies transferred to the morgue for judicial autopsy. Secondary clinical outcomes will be assessed in hospital before patient discharge; red cell AChE will be measured in a subset of patients by a laboratory blind to allocation.

### Study hypotheses and planned analyses

The main hypothesis is that multiples gastric lavages will reduce the case fatality rate from 15% to 9%, hence the primary comparison will be of multiple lavages with a single lavage.

It is possible that multiple lavages will be more effective the earlier they are started. Therefore we will assess the trends in clinical effectiveness according to time post-ingestion to start of therapy. In order to determine whether treatment should be started irrespective of severity, we will also assess trends in case fatality rates across a gradient of severity.

Subgroup analyses are planned to look at the consistency of treatment effect across particular OPs that are common in China, eg. dichlorvos, phorate, dimethoate. Analyses will also be done to check whether ingestion of a meal within one hour of the ingestion affects outcome.

Admission blood and stomach content samples will be retrospectively analysed to determine the identity of the poison ingested. The primary analyses will then be repeated with correction for the identity of the poison. The time-dependent variations of OP level will be analysed in order to provide OP toxic kinetic data.

### Statistical analysis

The main analysis will be carried out on an intention-to-treat basis, using the chi squared test for the primary outcome (or Fisher's exact test if appropriate) and for other dichotomous outcomes. Relative risk (plus risk reduction), absolute risk reduction and number needed to treat (plus 95% confidence intervals) will also be calculated. For outcomes where time-to-event is recorded, the log rank test will be used to compare treatment groups. In addition, a Kaplan-Meier curve will be produced to illustrate the comparison of mortality between groups.

An analysis of trends in treatment effect for factors 'reported time from ingestion to treatment' and 'patient status on admission' will also be performed using statistical modelling techniques.

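### Randomisation is stratified by admission coma score but the primary test and its intervals ignore the stratum, so they are conservative and some power is forgone

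*Protocol article*

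**What the plan says.** Under Allocation of patients, the protocol article says: "Stratified block randomisation will be performed according to patient status on admission". The two strata are Glasgow coma score 14–15 and below 14. No other stratification factor is named.

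Under Statistical analysis, the primary test is fixed by name: "The main analysis will be carried out on an intention-to-treat basis, using the chi squared test for the primary outcome", with Fisher's exact test as the alternative. On effect estimates it adds: "Relative risk (plus risk reduction), absolute risk reduction and number needed to treat (plus 95% confidence intervals) will also be calculated".

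Two other planned analyses come near the point. The first is in the same section: "An analysis of trends in treatment effect for factors 'reported time from ingestion to treatment' and 'patient status on admission' will also be performed". The second is under Study hypotheses and planned analyses: "The primary analyses will then be repeated with correction for the identity of the poison".

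**The concern.** Neither of those two analyses brings coma score into the primary comparison. The trend analysis asks whether the treatment effect varies with admission status, which is an interaction question, and it runs beside the main test. The one planned correction of the primary analysis is for the poison, not for coma score. The factor that constrained the allocation is therefore absent from the primary test and from the relative risk, absolute risk reduction and number needed to treat.

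Stratified allocation forces the arms to have nearly the same coma-score mix, so differences in death rate between strata no longer add noise to the treatment comparison. The crude variance p(1 − p) still counts that noise. The standard error is then too large by an amount that grows with how strongly coma score predicts death.

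Two things are at stake. At 454 per arm there is little spare power, and some is available without enrolling anyone. The Background also says that a finding of no benefit may lead to a trial of lavage against none, and needlessly wide intervals make that finding harder to read.

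**Working it through.** **Inputs from the protocol article.** Control mortality 15%, target 9% (relative risk 0.09/0.15 = 0.6), alpha 5%, power 80%, 454 per arm, 908 in total (Sample size); 1:1 allocation within two coma-score strata (Allocation of patients).

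**Reproducing the stated sample size.** Two-sided, without continuity correction:
- Pooled variance: n = [1.96·√(2·0.12·0.88) + 0.8416·√(0.15·0.85 + 0.09·0.91)]² / 0.06² = (0.9007 + 0.3851)² / 0.0036 ≈ 459.3, so 460.
- Unpooled variance: 7.849·0.2094/0.0036 ≈ 456.5, so 457.
- Arcsine: 453.7, so 454, the stated figure.

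The number was thus sized for an unstratified comparison. The ordinary formula gives 79.5% power at 454 per arm.

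**Inputs that have to be assumed.** The documents give neither the share of patients in each stratum nor their death rates. Three control-arm scenarios near 15% overall are used:
- Weak: 60% of patients at score 14–15 with 10% mortality, 40% below 14 with 22.5%.
- Middle: 65% with 5%, 35% with 33.6%.
- Strong: 70% with 4%, 30% with 41%.

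**Closed form under no treatment effect.** Let w be the share below 14, and p₁ and p₂ the death rates below 14 and at 14–15. Total variance per patient is T = p(1 − p), with p = w·p₁ + (1 − w)·p₂. The between-stratum part is B = w(1 − w)(p₁ − p₂)². With balance in each stratum the true variance is proportional to T − B, while the crude test uses T. Hence the crude standard error is too large by the factor k = √[T/(T − B)], and the crude test's true alpha is 2·[1 − Φ(1.96·k)].

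| Scenario | p | B | T | k | 1.96·k | True alpha |
|---|---|---|---|---|---|---|
| Weak | 0.1500 | 0.00375 | 0.12750 | 1.015 | 1.989 | 4.7% |
| Middle | 0.1501 | 0.01861 | 0.12757 | 1.082 | 2.121 | 3.4% |
| Strong | 0.1510 | 0.02875 | 0.12820 | 1.135 | 2.225 | 2.6% |

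The standard error is therefore about 1.5%, 8% and 13.5% too large when there is no effect. At a relative risk of 0.6 the excess is somewhat smaller, because lower death rates in the treated arm shrink its between-stratum part to 0.36·B. In the middle scenario the treated arm has T = 0.0901·0.9099 = 0.0819 and B = 0.0067. The factor is then √[(0.1276 + 0.0819)/(0.1090 + 0.0752)] ≈ 1.07.

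**Power by simulation.** 200,000 trials per scenario, 908 patients, exact 1:1 balance in each stratum, common relative risk 0.6, two-sided 5%:

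| Scenario | Crude chi-squared | Cochran-Mantel-Haenszel | Gain |
|---|---|---|---|
| Weak | 80.1% | 80.8% | 0.7 points |
| Middle | 81.4% | 84.5% | 3.1 points |
| Strong | 82.3% | 87.0% | 4.7 points |

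In the simulations the stratified test holds its 5% level. The crude test sits slightly above 79.5% because the balanced design makes the observed difference less variable than the sample-size formula supposes.

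**Effect of stratifying on the estimates.** With exact 1:1 balance in each stratum, the Mantel-Haenszel weight for the risk difference, n_C·n_T/(n_C + n_T), is proportional to stratum size. The stratified risk difference and relative risk then equal the crude ones, and only the standard errors change.

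**The case against.** The best defence is that nothing the plan promises is broken. Type I error stays below 5%, and the crude test reaches about 80% power in every scenario above. A crude test with simple risk measures is transparent and valid. This stands: a reader might infer that the mismatch inflates false positives or leaves the trial underpowered, and neither follows.

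The size is also uncertain. With no coma-score data in the documents, the loss could be close to nothing. That stands too, although the protocol itself treats admission status as a severity measure worth stratifying on.

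A condensed article may leave adjusted analyses to an analysis plan that is not shown. This carries less weight, because the article names the main test; a stratified primary test elsewhere would contradict it.

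It can also be said that a stratified summary presumes a common effect, while the plan looks for variation with severity. With balanced strata the stratified estimates coincide with the crude ones, so little is lost, and the trend analysis can still be done.

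Finally, a reader might infer that hospital is a second ignored stratum, because patients are randomised "using a dedicated handheld computer at each study hospital". The document does not support that. The phrase describes how allocations are delivered and does not establish separate lists by hospital. If hospital is not a stratum, omitting it does not make the standard error wrong, and chance imbalance between hospitals is already covered by the test's error rate.

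**Conclusion.** The point holds as a matter of efficiency and calibration, confined to coma score. The allocation is stratified and the stated primary analysis is not. If coma score predicts death, p-values and intervals are conservative. The direction is certain; the size rests on assumed stratum shares and death rates, and ranges from negligible to material across the three scenarios. The figures further assume a common relative risk of 0.6 and exact balance within strata. The stated block sizes of 3, 6 and 9 cannot all be split 1:1, so that balance is an idealisation. The planned error rate and power are preserved. This is a worthwhile improvement to a stated choice and does not make the trial invalid.

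**What to change.** Make the primary test a Cochran-Mantel-Haenszel test stratified by the randomisation stratum (coma score 14–15, below 14). Report the stratum-adjusted risk difference and relative risk with 95% confidence intervals, and derive the number needed to treat from the adjusted risk difference. Keep the crude chi-squared or Fisher's exact result as a sensitivity analysis. Add hospital as a stratum only if the allocation lists are in fact separate by hospital.

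The cost is wording in the protocol and analysis plan, settled before outcome data by arm are seen. Coma-score stratum is needed to randomise, so it is already recorded for every patient, and the sample size need not change.

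### The unadjusted log-rank rule leaves starting AChE and the coma-score stratum out of the comparison of red cell AChE recovery time, and loses power if starting activity is prognostic

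*Protocol article*

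**What the plan says.** The Statistical analysis section gives one rule for every time outcome: "For outcomes where time-to-event is recorded, the log rank test will be used to compare treatment groups". It names no covariate and no stratum. The Outcomes section lists, last of the secondary outcomes, "50% recovery time for red cell acetylcholinesterase enzyme activity". The rule does not mention AChE, so the link between the two is made by its general wording. No other method is offered for this outcome.

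On the data, the Sample size section says "red cell AChE will be measured in a subset of patients by a laboratory blind to allocation", without giving the size of the subset. The section on interventions and procedures says "A 10 ml blood sample will be taken using a sterile syringe and needle from each patient on recruitment" and, for a subset, "Further 5 ml blood samples will taken at one, four and twelve hours post-treatment, and then at daily intervals until discharge or death". Both arms receive the first lavage and part only later: "The above procedure will be repeated 4 hours and 8 hours after the first gastric lavage in the group of patients receiving multiple lavages". The article does not say that AChE is among the assays run on the recruitment sample.

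Allocation is stratified by Glasgow coma score (14–15 against below 14), not by AChE. The planned modelling concerns effect modification: "An analysis of trends in treatment effect for factors 'reported time from ingestion to treatment' and 'patient status on admission' will also be performed". The correction for poison identity applies to the primary analyses. Nothing planned brings starting AChE or the coma-score stratum into the comparison of recovery times.

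**The concern.** A recovery time is usually related to the depth from which recovery starts. If 50% means 50% of normal activity, a patient who starts just below that level has little to regain and one who starts near zero has much more. This spread between patients exists before the arms differ. A test that leaves it as noise is less able to detect an effect of the extra lavages.

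Two things are at stake: power on the only enzyme outcome, and the reading of the estimate if the two arms of the subset happen to start at different AChE levels. The coma-score stratum is a second baseline factor that the design treats as important and this analysis drops.

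**Working it through.** **1. The plan's own figure.** The only stated size is 454 per arm, for mortality of 15% against 9%. The arcsine formula reproduces it: h = 2·asin(√0.15) − 2·asin(√0.09) = 0.186, and n = 2 × (2.802 / 0.186)² ≈ 453.7, rounded up to 454. The unpooled formula gives 7.849 × (0.1275 + 0.0819) / 0.0036 ≈ 457. This figure stands and does not depend on the present point. No size is given for AChE.

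**2. Is a clean baseline available?** Blood is drawn from every patient on recruitment, and the arms diverge 4 hours after the first lavage. AChE assayed on that sample precedes any difference in treatment between the arms.

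**3. When would starting AChE be prognostic?** The article does not define the 50%.
- *50% of normal:* with linear recovery at rate r from starting activity a, time = (50 − a)/r, so the start enters directly. Assume starts spread evenly over 2–45% or 2–30% and recovery rates with a coefficient of variation of 0.5–1.5. The correlation with log recovery time then runs from −0.22 to −0.75.
- *Half-time of the patient's own recovery:* with first-order recovery, time = ln 2 / k, which does not depend on the start.

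**4. Scale of association.** For a proportional-hazards Weibull model with log-hazard β per SD of baseline, the size of the correlation with uncensored log time is β / √(β² + π²/6). This gives 0.36 for β = 0.5, 0.61 for β = 1 and 0.84 for β = 2. The first two lie within the range in step 3; the third lies beyond it.

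**5. Power.** All inputs are assumed: 100 patients in total, 1:1, 80 recoveries, 20% censored and hazard ratio 1.87. That hazard ratio gives 80% power if baseline is irrelevant: events = 4 × 7.849 / (ln 1.87)² ≈ 80. There were 500 runs per row, with a Monte Carlo standard error of about 2 points.

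| β per SD | Log-rank | Cox with baseline | Gain (points) |
|---|---|---|---|
| 0 | 78.6% | 77.2% | −1.4 |
| 0.5 | 71.0% | 79.4% | 8.4 |
| 1 | 45.8% | 78.4% | 32.6 |
| 2 | 20.8% | 76.8% | 56.0 |

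A second simulation assumed Weibull shape 1.3, recovery recorded in whole days, a 14-day limit, hazard ratio 1.5 and 400 runs per setting. It agrees:
- 100 per arm: 79% v 79% (β = 0), 63% v 79% (0.5) and 39% v 72% (1).
- 50 per arm: 37% v 48% (0.5) and 25% v 46% (1).

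Across both simulations the gain at β = 0.5 to 1 is 8 to 33 points. Neither includes the coma-score stratum, so its contribution is not sized.

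**6. Error rate and imbalance.** With no lavage effect (1000 runs per setting, first design), the log-rank test rejects in 4.4–5.6% of runs overall, which is nominal. Among runs with a baseline imbalance beyond 1.96 standard errors (about 5% of 1000, so some 50 runs per setting), it rejects in 2%, 10%, 20% and 35% for β = 0, 0.5, 1 and 2. The adjusted model rejects in 0–7%. With 100 patients such an imbalance is 1.96 × √(4/100) = 0.39 SD; with all 908 it would be 1.96 × √(4/908) = 0.13 SD.

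In the second design, with 100 per arm, no effect and β = 1, a 0.28 SD imbalance moves the average unadjusted hazard ratio to 1.22, with 21% of runs significant; adjusted, 5% are significant. Since 0.28 / √(2/100) = 1.98, that is an imbalance reached in about 1 trial in 20.

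**The case against.** The strongest reply is that nothing in the plan is invalid. Randomisation makes the unadjusted log-rank test sound, and chance imbalance is already paid for in the 5%. That stands. A reader might infer from the conditional rejection rates that the planned test is prone to false positives; the overall rates show that it is not.

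A reader might also infer that starting AChE largely determines the recovery time. The documents do not say so, and under the half-time reading of 50% it need not matter at all. It is likely to be prognostic under the threshold reading, and no more can be claimed.

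Nor do the documents support the view that each trial patient has a recruitment AChE value. Blood is taken from all, but AChE is measured in a subset and not expressly on that sample.

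The unadjusted hazard ratio is closer to 1 than the adjusted one (1.41 or 1.29 against 1.5 in the second simulation). This reflects a marginal against a conditional quantity and is not an error in the plan. It also seems natural to extend the point to later OP levels, but the article plans those for kinetic description and states no between-arm test.

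Finally, covariates for a laboratory secondary outcome are often settled in an analysis plan, and one may exist unseen. That limits the weight of the point. It does not remove it, because the article states the test and, for this outcome, names nothing beside it.

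**Conclusion.** The point holds as a matter of efficiency on one secondary outcome in a subset. The stated test is valid but discards baseline information that is obtainable before the arms diverge, and it leaves out the stratum used in randomisation. Under assumed log-hazards of 0.5 to 1 per SD, the loss is about 8 to 33 percentage points of power. With no association, adjustment costs 0 to 2 points, which is within simulation error. The estimate also remains exposed to whatever imbalance in starting AChE is seen, more so the smaller the subset.

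The size rests on assumptions that the documents neither give nor contradict: the subset size, the treatment effect, the censoring and the association of starting AChE with recovery. The mortality analysis and the 908 patients are not touched.

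**What to change.** In the Statistical analysis section, add for this outcome: recovery time will be compared by a Cox model with arm, the coma-score stratum and, for patients in the AChE subset, AChE activity assayed on the recruitment blood sample as a continuous covariate; the adjusted hazard ratio will be reported with its 95% CI. The unadjusted log-rank test may be kept as supportive. A log-rank test stratified by coma score is a simpler alternative, but it can use starting AChE only if that is banded.

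The cost is a sentence of text and one AChE assay per subset patient on blood already drawn, with no extra patient, visit or sample. The hazard ratio becomes conditional on the covariates and should be labelled so. All patients in the subset stay in the comparison whatever their starting level.
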